### Exploratory outcomes

The intervention guiding assessments MoCA [40], AMPS [41], and all neurocognitive assessments will be explored to describe rehabilitation needs at group level, knowledge that could guide clinicians and guide future development of interventions (see assessment timeline). Patient-reported data will be used to investigate the proportion of participants reporting modified job descriptions and job tasks.

### Strategies to improve adherence

The feasibility of the intervention has been tested and the intervention refined based on the gained experiences. As the study is a pragmatic study based on an individual assessment of the survivors’ expressed needs, the intervention is expected to be relevant for all participants. However, due to the single centre set-up transport to and from the study site could be a limiting factor to adherence. However, financial compensation for transport costs was offered to the participants. Furthermore, the intervention is designed to include relatives, and hence, the acceptability is expected to be relatively high, and relatives are therefore expected to be supportive and thereby increase the possibility of higher adherence to the intervention.

### Relevant concomitant care and interventions

Participants should continue to take any described medications. Irrespective of treatment allocation, participants should continue to participate in usual care activities, such as follow-up visits at the hospital or consultations with social workers. There are no restrictions regarding concomitant care during the trial.

### Criteria for discontinuing the trial

No criteria for discontinuing or modifying allocated interventions were imposed, but the survivor or their relatives could drop out of the intervention or withdraw their informed consent to participate in the study at any time, without consequences for the current or future treatment or specific for the allocated rehabilitation intervention. Should participants decide to withdraw from the trial, they will be asked if they agree that collected data, and explicit specific non-collected data form the registries, may be used for analysis.

### Recruitment, assignment of interventions, sequence generation, and allocation concealment

We will recruit trial participants directly from the cardiology ward. A study nurse at the ward will approach eligible survivors and invite them to participate in the present study. Participants will be randomly assigned to either the intervention or the usual care group using a computer random generator, with a 1:1 allocation by using varying block sizes. The randomisation will be conducted using the RedCap randomization module and will be stratified on sex (M/F) and age. Allocation concealment will be ensured as the randomization module block sizes are unknown, and the allocation will be locked after randomization. Clinical staff at the departments will obtain informed consent and enroll the participants. A named study author ([name], [name], or [name]) will randomize participants, and the clinical staff at the departments will inform the participants about the allocation and start the intervention based on standard operating procedures. The CONSORT flow diagram is presented in Fig. 2.

**Fig. 2 Fig2:**
[figure not shown]
Study flow diagram

### Blinding

Due to the nature of the intervention, neither participants, outcome assessors, nor staff conducting the intervention can be blinded to allocation. Group allocation will be anonymized before the data will be analysed by the data analysis responsible investigator to ensure blinding.

### Data management

All data will be handled and stored electronically in REDCap. All patient-reported and assessor-administered data entry will have checks for data values. Furthermore, all data points from assessor administered data will be cross-checked. Before extraction, all data will be anonymized, and group allocation will be blinded as group X and Y. Data will be enriched with DREAM data on labour market participation from the National Registry.

#### Statistical methods

A full statistical analysis plan will be uploaded prior to analysis at ClinicalTrials.gov (NCT05173740).

### Superiority margins

Superiority margin is set at 10%. Superiority will be claimed if confidence intervals are above 1, and a difference of 10% or more between the intervention group and the control group is detected.

### Sample size

The sample size calculation for the present trial is based on a study by Moulaert et al. who evaluated the effectiveness of a rehabilitation intervention on health-related quality of life for OHCA survivors but reported exploratory finding for RTW after 1 year. In that study, 71% of the control group had returned to work after 1 year. We expect the intervention to increase this by 25% corresponding to a RTW rate of 88.8%. Using the formula for large-sample tests for proportions in a two-sample parallel design with a superiority margin of 10% and a power of 80%, 85 survivors are needed in each arm, 170 in total. Based on the sample size calculation and an expected 20% dropout rate, 107 OHCA survivors are needed in each study arm, 214 in total [42].

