### Planned reporting

Participant’s characteristics are planned to be reported as outlined in Supplemental Table 2. The primary outcome will be reported as unadjusted and adjusted OR of RTW at 12 months (see Table 2). The multistate model will be reported as outlined in Table 5 and visualized using sequence analysis (see Table 3).

**Table 2 Tab2:** Unadjusted and adjusted OR of RTW at 12 months. Odds ratio (OR), 95% confidence interval (95% CI)

	Unadjusted OR RTW (95% CI)	Adjusted OR RTW (95% CI)
Intervention	OR (95% CI)	OR (95% CI)
Age	OR (95% CI)	OR (95% CI)
Male sex	OR (95% CI)	OR (95% CI)
Marital status	OR (95% CI)	OR (95% CI)
Occupation	OR (95% CI)	OR (95% CI)

**Table 3 Tab3:** Unadjusted and adjusted hazard ratio (HR) of RTW at 12 months. 95% confidence interval (95% CI). May include estimates from transient intensity matrix/HR from multistate models

	Unadjusted HR sick leave: full time (95% *CI*)	Adjusted HR sick leave: full time (95% *CI*)	Unadjusted HR sick leave: part time (95% *CI*)	Adjusted HR sick leave: part time (95% *CI*)
Intervention	HR (95% CI)	HR (95% CI)	HR (95% CI)	HR (95% CI)
Age	HR (95% CI)	HR (95% CI)	HR (95% CI)	HR (95% CI)
Sex	HR (95% CI)	HR (95% CI)	HR (95% CI)	HR (95% CI)
Marital status	HR (95% CI)	HR (95% CI)	HR (95% CI)	HR (95% CI)
Occupation	HR (95% CI)	HR (95% CI)	HR (95% CI)	HR (95% CI)
	Unadjusted HR part time: retired (95% *CI*)	Adjusted HR part time: retired (95% *CI*)	Unadjusted HR full time: retired (95% *CI*)	Adjusted HR full time: retired (95% *CI*)
Intervention	HR (95% CI)	HR (95% CI)	HR (95% CI)	HR (95% CI)
Age	HR (95% CI)	HR (95% CI)	HR (95% CI)	HR (95% CI)
Sex	HR (95% CI)	HR (95% CI)	HR (95% CI)	HR (95% CI)
Marital status	HR (95% CI)	HR (95% CI)	HR (95% CI)	HR (95% CI)
Occupation	HR (95% CI)	HR (95% CI)	HR (95% CI)	HR (95% CI)

Unadjusted and adjusted estimates for secondary end points will be reported as outlined in Supplemental Table 3. RTW at 6 months will be assessed with logistic regression, other variables with generalised linear mixed models. Results for PROMs will be reported for each subscale separately in text.

Furthermore, patient-reported RTW, the degree of RTW in hours weekly compared to prior to the cardiac arrest), changed job description, and modification in job task will be reported descriptively.

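### 85 per arm does not follow from 71% versus 88.8%, a 10% superiority margin and 80% power, and the success rule uses the 10% as a cut-off on the observed difference, not as a margin

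*Protocol article*

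**What the plan says.** The Sample size section of the protocol article takes its control rate from an earlier rehabilitation trial in cardiac arrest survivors, in which "71% of the control group had returned to work after 1 year". The effect is given as "We expect the intervention to increase this by 25% corresponding to a RTW rate of 88.8" per cent. The method is described as "Using the formula for large-sample tests for proportions in a two-sample parallel design", and the result is that "with a superiority margin of 10% and a power of 80%, 85 survivors are needed in each arm, 170 in total". A 20% dropout allowance raises this to 107 per arm, 214 in total.

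The Superiority margins section says "Superiority margin is set at 10" per cent. It then gives the success rule: "Superiority will be claimed if confidence intervals are above 1, and a difference of 10% or more" between the groups must be detected.

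Planned reporting adds that "The primary outcome will be reported as unadjusted and adjusted OR of RTW at 12 months", with 95% confidence intervals in Table 2. The article gives no alpha or sidedness for the sample size, and does not say whether the 10% is absolute or relative.

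**The concern.** A superiority margin in a sample size calculation shifts the null hypothesis: the trial must show that the effect exceeds the margin, so the distance left to detect is the expected effect minus the margin. Here the expected difference is 88.8 − 71 = 17.8 points. A 10-point margin leaves 7.8 points, which 85 per arm cannot detect with 80% power.

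The success rule does not shift the null. It compares the interval with 1, which is no effect, and applies the 10% to the observed difference. The same 10% therefore has two meanings in adjacent sections. At stake is what a positive primary result may be said to show, and whether the stated power belongs to the test that will be done.

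**Working it through.** **Inputs.** Rates of 71% and 88.8% (0.71 × 1.25 = 0.8875 before rounding), the 10% margin and 80% power come from Sample size and Superiority margins. Allocation is 1:1 (recruitment and assignment section). Two-sided 5% is an assumption taken from the 95% intervals in Table 2; one-sided 5% is shown as the range.

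**1. Can 85 be reproduced?** (z₀.₉₇₅ + z₀.₈₀)² = (1.960 + 0.842)² = 7.849.

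- Difference in proportions, no margin: 7.849 × [0.71×0.29 + 0.888×0.112] / 0.178² = 7.849 × 0.3054 / 0.03168 = 75.6, so 76 (79 with a pooled variance).
- Log odds ratio, no margin: 7.849 × [1/(0.71×0.29) + 1/(0.888×0.112)] / (ln 3.238)² = 7.849 × 14.91 / 1.381 = 84.8, so 85. At the unrounded 88.75% it is 85.3.
- Difference in proportions, 10-point margin, with 25% entered as 25 percentage points (71% versus 96%): 7.849 × [0.71×0.29 + 0.96×0.04] / (0.25 − 0.10)² = 85.2. Power at exactly 85 is 79.9%.

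Two routes therefore lead to 85. One uses no margin and a scale that the section does not name. The other uses the margin but an intervention rate of 96%, which contradicts the stated 88.8%. The dropout step is correct: 85 / 0.8 = 106.25, so 107.

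**2. Sample size with the stated rates and a margin m.** n = (z_α + z_β)² × [p₁(1−p₁) + p₂(1−p₂)] / (p₂ − p₁ − m)². Ranges run from p₂ = 88.8% to p₂ = 88.75%.

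| Margin | Two-sided 5% | One-sided 5% |
|---|---|---|
| 10 points | 7.849 × 0.3054 / 0.078² = 393.9; range 394 to 400 | 310 to 315 |
| 10% of 71% = 7.1 points | 7.849 × 0.3054 / 0.107² = 209.3; range 209 to 212 | 165 to 167 |

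**3. Power of the planned numbers.** At 85 per arm the standard error is √(0.3054/85) = 0.0599. For a 10-point margin, power is Φ(0.078/0.0599 − 1.960) = 25.5%.

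| Margin | n per arm | Two-sided 5% | One-sided 5% |
|---|---|---|---|
| 10 points | 85 | 25.5% | 36.6% |
| 10 points | 107 | 30.9% | 42.7% |
| 7.1 points | 85 | 43.1% | 55.6% |
| none (pooled variance) | 85 | 83.1% | – |

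**4. The success rule as written.** All binomial outcomes were enumerated, with the 95% interval of the unadjusted odds ratio standing in for the adjusted one and the 10% read as 10 points. Entries are the probability of claiming superiority.

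| True rates | n per arm | Interval above 1 | Interval above 1 and observed difference ≥ 10 points | Lower 95% limit of difference above 10 points |
|---|---|---|---|---|
| 71% vs 88.8% | 85 | 83.5% | 83.5% | 25.8% |
| 71% vs 81% | 85 | 32.4% | 32.4% | 2.6% |
| 71% vs 71% | 85 | 2.5% | 2.5% | 0.04% |
| 71% vs 88.8% | 107 | 91.2% | 91.2% | 31.3% |

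The cut-off removes almost nothing because, with about 71% in the control arm, an observed difference must already reach about 12.9 points (85 per arm) or 12.1 points (107 per arm) to be significant.

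**The case against.** The best defence is that the rule is a legitimate dual criterion. Requiring an interval above 1 plus a minimum observed difference is stricter than significance alone and cannot inflate the type I error; the third row of the last table shows 2.5%. This stands. The fault lies in the label, the unstated scale and the mismatch with the sample size text, not in having two conditions. Nor is the difference unobtainable because odds ratios are the planned output: the crude difference needs only the two arm proportions.

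A second defence is that 10% might mean a ratio. A risk-ratio margin of 1.10 needs 255 per arm (201 one-sided). An odds-ratio margin of 1.10 needs 101 (80 one-sided), which brackets 85 without giving it. But the article names a formula for proportions and speaks of a difference between groups, so it does not support the odds-ratio reading.

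A third is that a full analysis plan is promised. It can add detail, but it cannot make 85 correct for inputs fixed here.

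A reader might infer from the exact match on the log odds ratio scale that no margin was used. The document does not establish this. The formula it names gives 76 without a margin, and a mis-entered effect with the margin also gives about 85. Only the sponsor can say which occurred.

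**Conclusion.** The stated sample size is wrong for its stated inputs. On either difference-scale reading of the 10%, and at one- or two-sided 5%, the requirement is about two to almost five times 85 per arm. Power at 85 per arm is about 25% (37% one-sided) for a 10-point margin and 43% (56%) for a 7.1-point margin. At 107 per arm it is 31% (43%) for 10 points. These figures rest on the assumed alpha, which the article does not give.

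The success rule is in practice a test of no effect. At the design rates the 10% condition changes nothing, and with a true difference of exactly 10 points the rule still succeeds about 32% of the time at 85 per arm. A positive result would therefore support an effect above zero, not superiority by at least 10%.

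A reader might go further and conclude that the trial is too small for its primary comparison. The figures do not support that: as a conventional zero-margin comparison at the stated rates, 85 per arm has about 83% power.

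**What to change.** State alpha, sidedness, the formula used and the scale of the margin; establish how 85 was obtained; and make the Sample size and Superiority margins sections agree. Two routes are open:

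- **No margin.** Describe the sample size as a two-sided 5% superiority test against no effect, for which 85 per arm gives about 83% power at 71% versus 88.8%, and stop calling the 10% a superiority margin.
- **True margin.** Keep it, test against it, and restate the power at 85 per arm as about 25% (37% one-sided) for 10 points, or the corresponding figure for the scale chosen.

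Whether to keep the condition on the observed difference is the sponsor's choice. If it is kept, label it a minimum observed difference, say whether it is absolute or relative, and report the marginal risk difference with its 95% interval from the logistic model beside the odds ratio.

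The cost is wording and one extra estimate from the planned model; neither route needs more patients. On the first route the stated claim becomes less ambitious: a difference above zero, not above 10%. The Protocol amendments section already provides for registering and justifying such a change, which should be made before the analysis.

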### Primary outcome

The primary outcome will be analysed using logistic regression assessing RTW status at 12 months adjusting for the intervention and age at OHCA, sex, marital status, and occupation prior to OHCA. Patient-reported data on return-to-work will be used to enrich the analysis (e.g. self-employed persons, activation of substantial self-regulated pensions, unemployed without social transfer payment).

Sequence analysis will visualize how survivors change states during the follow-up time [43, 44] but also describe time spent in each state (working vs. social transfer benefit, etc.) and order of states during follow-up. However, sequence analysis is exploratory and cannot answer hypotheses or be adjusted for covariates.

Because return to work is complex, transitions between work states will be explored further. Multistate models can be used to assess influences from covariates on transitions between stages, e.g. from working to social transfer benefit, or reverse, or from working until death.

Retirement is an important state in this setting; however, retirement to private pensions is not registered in the DREAM database [20]. Thus, a multistate model including this important state will have to be built using data from survivors’ questionnaires. This is possible, as retirement is an absorbing state see (Supplemental Figure 1).

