## Background

Each year, more than 5000 citizens experience an out-of-hospital cardiac arrest (OHCA) in Denmark. In 2021, the Danish 30-day survival rate was 13% equivalent to yearly incidence of 610 OCHA survivors [1].

Rehabilitation targeting physical, neurological, and psychological consequence after OHCA is recommended in international clinical guidelines. Due to hypoxic–ischaemic brain injury, the course of acute post-cardiac arrest care and the trauma of resuscitation the frequency of cognitive impairment and emotional reactions are high in survivors of cardiac arrest. These problems affect survivors and restrict their ability to return-to-work (RTW) [2, 3]. Although the majority of cardiac arrest survivors are classified with mild to moderate cognitive impairment, roughly 50% experience long-term neurocognitive impairment. Thus, most cognitive recovery is found to occur during the first 3 months after resuscitation [4, 5]. Looking at emotional issues, both depression, anxiety, and post-traumatic stress disorder are found to affect approximately 20–25% of survivors in the long term [6]. Overall, these neuropsychological postarrest challenges complicate participation in society and are associated with social issues such as failure to resume social activities and impaired RTW [3, 6, 7]. A Danish nationwide cohort study by Jørgensen and colleagues investigated RTW and the subsequent detachment from employment in cardiac populations [8]. The authors found high probabilities of not returning to work, in patients diagnosed with heart failure. These results are in line with our previous findings [2]. Six months after resuscitation, we found 58% of survivors on full-time sick leave or working notable less (10 h/week) compared to prior to the cardiac arrest. In addition, an extensive part of those who had RTW had changed job descriptions or had been assigned less demanding job tasks. Other resuscitation research support these findings, as they found that flexible work hours and/or modified job descriptions were offered to 74% of participants in a register-based OHCA population [9].

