### Usual care

All participants including those allocated to the usual care group will be seen by an occupational therapist if their MoCA screening score ≤ 26. Furthermore, if considered relevant by the discharging unit, survivors are referred for rehabilitation provided and delivered in the local municipality where the participant is resident. The content of the rehabilitation will typically be based on the content of the rehabilitation plan from the discharging hospital unit and an individual assessment of the survivors’ expressed needs, within the local municipality where the participant is resident.

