**Table 1 Tab1:**
[figure not shown]
SPIRIT figure. Schedule of enrolment, allocation, interventions, and assessments

*t*_1_ 2 weeks, *t*_2_ 6 weeks, *t*_3_ 12 weeks, *t*_4_ 26 weeks, *t*_x_ 52 weeks (primary endpoint). Readiness for return to work (*RRTW*), Multidimensional Fatigue Inventory (*MFI-20*), the 5-level EuroQol-5 domain (EQ-5D-5L) quality-of-life questionnaire, European quality-of-life survey (HeartQoL), the Pittsburgh Sleep Quality Index (PSQI), Health Literacy Questionnaire (HLQ), and Impact of Event Scale-Revised (IES-R). Intervention group only. Sequence analysis of labour market trajectories using data registered in the DREAM database. Only participants allocated to the intervention, §¤list of tests; Trail making A, Trail Making B, digit span forwards, digit span backwards, RBANS list learning, RBANS story memory, Rey’s complex figure test — copy, coding, Rey’s complex figure test, immediate recall, letter number sequencing, design fluency, RBANS list recall, RBANS list recognition, RBANS memory recall, block design, verbal fluency Test (animals), verbal fluency test (S-words)

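### The primary model adjusts for no cognitive measure, although a MoCA score appears to exist in both arms; if it is taken before allocation, adding it would gain some precision

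*Protocol article*

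**What the plan says.** The covariate set is fixed in three places of the protocol article: the Abstract, the Primary outcome text under Statistical methods, and the shell of Table 2. The Primary outcome text states: "The primary outcome will be analysed using logistic regression assessing RTW status at 12 months adjusting for the intervention and age at OHCA". The remaining covariates named there are occupation before the arrest, marital status and sex. None of the three places contains a cognitive measure.

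MoCA appears elsewhere. The Usual care section makes one contact in both arms depend on it: "All participants including those allocated to the usual care group will be seen by an occupational therapist if their MoCA screening score ≤ 26". Under Exploratory outcomes: "The intervention guiding assessments MoCA [40], AMPS [41], and all neurocognitive assessments will be explored to describe rehabilitation needs at group level". That group-level description is the only analytic use of MoCA that the article states; the same sentence also presents MoCA as a guide to the intervention.

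On cognition and the outcome, the Background says that "these neuropsychological postarrest challenges complicate participation in society and are associated with social issues such as failure to resume social activities and impaired RTW". It puts long-term neurocognitive impairment at roughly half of survivors.

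Randomisation "will be stratified on sex (M/F) and age". Both of these factors are in the primary model.

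**The concern.** The article names cognition as a reason why survivors fail to return to work, appears to measure it in everyone, and then leaves it out of the primary analysis. Marital status is in the model without any comparable rationale. Cognition is not a stratification factor either, so its balance between arms is left to chance. The article accepts the general principle elsewhere: the section on checking assumptions adjusts the final repeated-measures model for baseline values.

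What is at stake is efficiency. Adjusting a logistic model for a prognostic baseline value raises the power of the treatment test and takes account of whatever chance imbalance arises. If the score is already collected before allocation, this needs no new data.

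**Working it through.** **Inputs from the article (Sample size).** Return to work 71% in control and 88.8% with the intervention; 80% power; 85 per arm before dropout and 107 after 20% dropout.

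**Assumptions, not in the article.** A two-sided 5% test. MoCA standardised and normally distributed, with an odds ratio for return to work of 1.5 to 3 per SD. No 10% margin. Age, sex, marital status and occupation not modelled.

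**1. The plan's own figure.** The log odds ratio is ln(0.888/0.112) − ln(0.71/0.29) = 1.175, an odds ratio of 3.24. Its variance for one participant per arm is 1/(0.71 × 0.29) + 1/(0.888 × 0.112) = 14.91. Without a margin, n = 14.91 × (1.960 + 0.842)² / 1.175² = 84.8, so 85 per arm. Dropout: 85/0.80 = 106.25, so 107. The stated 10% margin does not lead to 85: a test of the difference in proportions against that margin needs 394 per arm two-sided or 311 one-sided. That is a separate and larger problem. Here it means only that the power figures below are for a test without a margin.

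**2. Power with and without MoCA.** 8,000 simulated trials per setting, with the arm intercepts set so that the marginal rates stay at 71% and 88.8%.

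| Odds ratio per SD | 85 per arm: without → with | 107 per arm: without → with |
|---|---|---|
| 1 (no association) | 84.2% → 83.9% | 90.9% → 90.8% |
| 1.5 | 83.5% → 84.5% | 91.6% → 92.1% |
| 2 | 83.3% → 85.3% | 90.7% → 92.5% |
| 2.5 | 82.8% → 87.1% | 91.1% → 93.9% |
| 3 | 84.1% → 89.0% | 91.3% → 94.8% |

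From 1.5 to 3 the gain is 1.0 to 4.9 points at 85 per arm and 0.5 to 3.5 points at 107. The first row shows a loss of 0.1 to 0.3 points when MoCA predicts nothing.

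**3. Chance imbalance.** The standard error of the difference in mean MoCA between arms is sqrt(2/85) = 0.153 SD. At an odds ratio of 2 per SD, an imbalance of one standard error shifts the log odds ratio by about 0.153 × ln 2 = 0.106. The standard error of the treatment log odds ratio is sqrt(14.91/85) = 0.419, so the shift is 0.106/0.419 = 0.25 of a standard error, or 0.106/1.175 = 9% of the planned effect.

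**4. Room for one more parameter.** Expected participants not back at work: 85 × (0.29 + 0.112) = 34, or 107 × 0.402 = 43. The present model has at least five parameters besides the intercept. A sixth takes events per parameter from 34/5 = 6.8 to 34/6 = 5.7, or from 43/5 = 8.6 to 43/6 = 7.2.

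**5. Timing.** The Usual care section does not date the MoCA screening. The body of Table 1 is not visible. Its footnote restricts some items to one arm: "Only participants allocated to the intervention, §¤list of tests; Trail making A, Trail Making B". MoCA is not among the tests listed there, but the rows to which the restriction applies cannot be read. Measurement in both arms before allocation is therefore an inference.

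**The case against.** The strongest reply is that nothing here is wrong. The model is prespecified and contains both stratification factors, and the article nowhere promises adjustment for cognition. That stands: the point is an improvement and not a correction of an error.

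Three stronger readings are tempting, and the article supports none of them.

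- **MoCA is the strongest baseline predictor.** The Background gives only a qualitative link, for cognitive and emotional problems together, with no effect size and no ranking against age or occupation. It also places most cognitive recovery in the first three months, so an early score may predict 12-month status only modestly.
- **Omission biases the result.** Randomisation balances cognition in expectation, and the confidence interval already allows for chance imbalance. What is lost is precision.
- **MoCA serves only for referral and description.** It is also said to guide the intervention.

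Two further objections limit the size. The simulation leaves out the planned covariates, so any overlap between MoCA and age or occupation would shrink the gain. It also ignores the 10% margin and so does not give power for the stated success rule. Both stand. The cost of a further parameter is real too, but small next to a model that already has five or more.

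**Conclusion.** The point holds as a conditional efficiency improvement. The primary model leaves out a measure that the article itself connects with return to work and appears to collect in both arms. The gain from adding it is modest: about 1 to 5 power points at 85 per arm and 0.5 to 3.5 at 107. These figures rest on an assumed odds ratio of 1.5 to 3 per SD, a two-sided 5% test without the 10% margin, and no other covariates. The validity of the randomised comparison is not in question. The whole point depends on the score being taken before allocation in both arms, which the visible text does not establish.

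**What to change.** First confirm from the full schedule when MoCA is taken and in whom.

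- **If before allocation in both arms:** prespecify the score as one continuous covariate in the primary logistic model and add a row to Table 2. Do not dichotomise it at 26. The article's fallback for non-linear variables allows transformation or categorisation; for MoCA, name transformation. Impute missing baseline scores without regard to arm, so that nobody is dropped. Keep the present covariate set as a sensitivity analysis. The two odds ratios will differ somewhat even with perfect balance, because the odds ratio is not collapsible: at an odds ratio of 2 per SD, the simulated marginal 3.24 corresponds to a conditional 3.53.
- **If after allocation:** do not use it as a covariate.

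The change must be made before unblinding. The article leaves room for this: the full analysis plan is to be uploaded before analysis, amendments are registered and justified, and the last visit is anticipated at the end of 2026.

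The cost is one line in the analysis plan, one table row, one more parameter with roughly 34 to 43 expected participants not back at work, and a few scores to impute.
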